## Abstract

**Background:** An increasing body of research highlights reconsolidation-based therapies as emerging treatments for post-traumatic stress disorder (PTSD). The Rewind Technique is a non-pharmacological reconsolidation-based therapy with promising early results, which now requires evaluation through an RCT.

**Objectives:** This is a preliminary efficacy RCT to determine if the Rewind Technique is likely to be a good candidate to test against usual care in a future pragmatic efficacy RCT.

**Methods:** 40 participants will be randomised to receive either the Rewind Technique immediately, or after an 8 week wait. The primary outcome will be PTSD symptom severity as measured by the Clinician-Administered PTSD Scale for DSM5 (CAPS-5) at 8 and 16 weeks post-randomisation. Secondary outcome measures include the PTSD Checklist (PCL-5), International Trauma Questionnaire (ITQ), Patient Health Questionnaire (PHQ-9), the General Anxiety Disorder-7 (GAD-7), Insomnia Severity Index, the Euro-Qol-5D (EQ5D-5 L), the prominence of re-experiencing specific symptoms (CAPS-5) and an intervention acceptability questionnaire to measure tolerability of the intervention.

**Conclusions:** This study will be the first RCT to assess the Rewind Technique. Using a cross-over methodology we hope to rigorously assess the efficacy and tolerability of Rewind using pragmatic inclusion criteria. Potential challenges include participant recruitment and retention.

**Trial registration:** ISRCTN91345822

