Some reconsolidation approaches have yielded negative results (Bos, Beckers, & Kindt, 2014; Wood et al., 2015) highlighting the specific limitations which exist around the ability of a therapy to destabilise and modify a traumatic memory. These factors, such as the length of the memory reactivation procedure and the age and context of the traumatic memory, are known as boundary conditions (Treanor, Brown, Rissman, & Craske, 2017) and have complicated the process of translation from experimental into clinical settings. Promising preliminary evidence, however (Adams & Allan, 2018; Utuza, et al., 2012), suggests that if reconsolidation is the mechanism of action for the Rewind technique, that these conditions may have been met.

While trauma-focused psychotherapies (TFCBT, EMDR) have medium to large effect sizes, the therapy requires large amounts of therapist time (Lewis et al. 2020). We expect that Rewind will have a similar effect size, but be more time and cost efficient, delivering a trauma-focused intervention in just a few sessions. Furthermore, as Rewind is relatively simple to deliver it has potential to be delivered by lower intensity therapists and therefore is more easily scalable. Furthermore, evidence of multiple effective therapies also provides treatment choice for people with PTSD, e.g. some individuals may prefer Rewind as it does not require trauma disclosure. Considering this, Rewind may be most suitable as a first-line intervention as part of a stepped care approach.

Given the promise of non-pharmacological approaches to the treatment of PTSD through the mechanism of memory reconsolidation, we aim to undertake a preliminary efficacy RCT to determine if the Rewind Technique is likely to be a good candidate to test against usual care in a future pragmatic efficacy RCT. Our objectives are:

1. To investigate the effect sizes of the Rewind Technique at reducing PTSD symptoms in people with PTSD.

2. To establish whether any symptom improvement is maintained over 16 week follow up.

3. To investigate the impact of the Rewind Technique on symptoms of depression, anxiety and insomnia.

4. To investigate if an efficacy RCT is feasible and indicated.

5. To assess if the Rewind Technique is acceptable to participants with PTSD as measured by a qualitative questionnaire.

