### Study design

2.1.

The study will be a two-armed, phase 2 exploratory RCT to assess the preliminary efficacy, adherence, feasibility and factors affecting outcome of the Rewind Technique versus a waitlist control group (Table 1).

**Table 1. t0001:** Gantt chart illustrating study timeline

[figure not shown]

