### Outcome measures

2.6.

A trained member of the research team, blind to randomization, will conduct all clinical assessments. It is not possible for therapists or participants to be blind to treatment allocation, but participants will be asked not to discuss their allocation with their assessor. An initial telephone screen will confirm that the participant meets the inclusion criteria. To ensure they consistently meet the inclusion criteria, participants will be asked to monitor their symptoms for two weeks, at which point we will take informed consent, collect baseline demographic data, outcome measurements, reassess eligibility, and then randomise eligible individuals to one of two groups using a computer programme: the Rewind Technique immediately or a waitlist for eight weeks followed by the Rewind Technique. We will monitor change in PTSD, depressive and anxiety symptoms using the PTSD Checklist (PCL-5), Patient Health Questionnaire (PHQ-9), and General Anxiety Disorder-7 (GAD-7) at the start of each treatment session. Follow-up and repeated collection of outcome data will occur 8 and 16 weeks post-randomisation.

The primary outcome of PTSD symptom severity, and PTSD diagnosis will be measured by trained assessors using the Clinician Administered PTSD Scale for DSM-5 (CAPS-5) (Weathers et al., 2018). The CAPS-5 is widely referred to as the gold standard in PTSD assessment, demonstrating high internal consistency (α =.88) and strong test-retest reliability (к = .83) (Weathers et al., 2018). Measuring DSM-5 PTSD allows comparability with previous psychological therapy RCTs.

Secondary outcomes, collected at 8 and 16 weeks will include:

The PTSD Checklist (PCL-5), a validated and widely used self-report measure for DSM-5 PTSD symptoms (Ruggiero, Del Ben, Scotti, & Rabalais, 2003).

The International Trauma Questionnaire (ITQ), a validated self-report measure for ICD-11 PTSD and complex PTSD (Cloitre et al., 2018).

The Patient Health Questionnaire-9 (PHQ-9), a validated and widely used self-report measure for assessing DSM-5 depressive symptoms (Kroenke, Spitzer, & Williams, 2001).

The Generalised Anxiety Disorder Assessment-7 (GAD-7), a validated and widely used self-report measure for assessing symptoms of generalised anxiety disorder (Spitzer, Kroenke, Williams, & Lowe, 2006).

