### Intervention

2.7.

*The Rewind Technique –* This will comprise up to three 60-minute sessions following a protocol developed by [name] (Muss, 1991) which has been modified by [name] and the research team following feedback from therapists. The intervention will be administered by experienced and trained psychological therapists under the supervision of [name] and the Cardiff and Vale University Health Board Traumatic Stress Service. The participant will be introduced to the technique and the theory behind it before being asked to imagine he/she is in a cinema watching a film of her/his traumatic event as if it had been captured on CCTV. Rather than the film start at the trauma itself the person with PTSD is told the film starts just before the traumatic event took place and is then followed by the regular intrusive recall which includes all the images, sounds and smells plus (if this is part of the regular recall) what could have happened next but didn’t. Once the recall ends, the sufferer is (metaphorically) invited to enter the screen and at that point the film is rewound at speed back to the exact starting point (where all was well before the trauma). The forward part of the process of recalling the trauma should not take longer than 2 minutes, the rewind part about 10 seconds. This usually requires the person with PTSD to practise the technique a few times before feeling confident it is being undertaken as intended.

*Wait list* – The wait list group will receive no intervention for 8 weeks after randomisation, at which point they will then receive the Rewind Technique in the same manner as the immediate treatment group.

Participants will be randomised to receive either the Rewind Technique or wait list using a 1:1 ratio.

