### Planned analyses

2.9.

We will conduct intention-to-treat analyses on all randomised participants. We will compare the means of continuous data using ANCOVA with baseline outcomes (such as CAPS-5 score) as co-variates. Risk ratios will be calculated for categorical data. The factors associated with reduction in symptom severity scores will be analysed using regression (baseline CAPS-5 score, age, prominence of re-experiencing symptoms, depressive symptoms, educational attainment and employment status), with all analyses performed at the end of data collection using SPSS. The dataset will be cleaned and then ‘locked’ before the randomisation codes are revealed and the final analyses undertaken. This will ensure those conducting the analysis are blind to condition.

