## Discussion

3.

This phase 2 exploratory trial will assess the preliminary efficacy, acceptability and feasibility of the Rewind Technique to determine if an effectiveness RCT is indicated. If a phase 3 RCT is warranted, investigating possible effect sizes of the intervention in this trial will enable us to conduct an appropriate power calculation. This will be the first RCT evaluating Rewind, with previous non-randomised work highlighting the need for randomised trials, particularly those with long term follow up (Adams & Allan, 2018). Previous pilot work has assessed outcomes 2 weeks post-intervention, while we will follow-up participants 8 and 16 weeks post-randomisation. While RTM has been investigated in randomised trials and shares many characteristics with Rewind (Gray, 2011), it is fundamentally a different intervention and both require evaluation separately.

We will also improve on previous research by using the ‘gold standard’ of PTSD assessment, the CAPS-5, to measure our primary outcome. Previous pilot work shows the intervention to be well tolerated (Adams & Allan, 2018), and our involvement of patient and public representatives in the production of our participant information sheets, consent forms and trial protocol aims to improve the acceptability of recruitment and the intervention itself. Furthermore, considering the urgent need for new treatments for PTSD, and the current prevalence of Rewind already as a therapy in the UK (IARTT (International Association for Rewind Trauma Therapy), 2019), new evidence is clearly needed to assess the long-term effectiveness of Rewind on symptoms of PTSD, anxiety, depression and insomnia. While this trial is not powered to definitively assess effectiveness, it will provide the highest quality of evidence available for the Rewind technique.

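### The abstract gives CAPS-5 at weeks 8 and 16 equal primary rank, but the waitlist arm is treated from week 8, so only week 8 compares Rewind with waitlist

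*Protocol article*

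**What the plan says.** The abstract of the protocol article defines the primary outcome with two time points and no order between them: "The primary outcome will be PTSD symptom severity as measured by the Clinician-Administered PTSD Scale for DSM5 (CAPS-5) at 8 and 16 weeks post-randomisation". Section 2.6 (Outcome measures) names CAPS-5 severity as primary without attaching a time to it, and says of data collection: "Follow-up and repeated collection of outcome data will occur 8 and 16 weeks post-randomisation".

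Section 2.1 (Study design) sets out the comparison: "feasibility and factors affecting outcome of the Rewind Technique versus a waitlist control group". Section 2.7 (Intervention) leaves the waitlist arm untreated for 8 weeks, "at which point they will then receive the Rewind Technique in the same manner as the immediate treatment group". The intervention is at most three sessions of 60 minutes.

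Objective 2, at the end of section 1, reads: "To establish whether any symptom improvement is maintained over 16 week follow up". The one analysis given for means is in section 2.9 (Planned analyses): "We will compare the means of continuous data using ANCOVA with baseline outcomes (such as CAPS-5 score) as co-variates". It names no visit and no contrast. The Discussion treats both visits as follow-up of participants in general ("while we will follow-up participants 8 and 16 weeks post-randomisation") and says of a later phase 3 trial that "investigating possible effect sizes of the intervention in this trial will enable us to conduct an appropriate power calculation".

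**The concern.** One of the two primary time points falls after the control arm has been offered the treatment under test. At that visit there is no untreated group, so a difference between the arms is no longer an effect against waitlist. The abstract calls the method a cross-over, but only one arm changes condition, so there is no second controlled period to make up for this.

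If both time points stand as primary, the trial will report two primary results that answer different questions. A week-16 difference near zero could be taken as failure of Rewind, or as loss of its effect, when it is also what lasting success in both arms would produce. The same ambiguity reaches the effect size for a later trial, since two primary values leave open which one is meant.

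**Working it through.** **Inputs from the article.** Primary times: weeks 8 and 16 (Abstract). Waitlist arm treated from week 8 (2.7). Effect size regarded as clinically relevant: 1.45 SD (2.3). Randomised: 20 per arm with 25% attrition (2.3), so 20 × 0.75 = 15 completers per arm.

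The plan gives no figure for a week-16 contrast, so there is none to reproduce on this point. The stated 15 per arm does not follow from Lehr's formula at an effect size of 1.5 (16/1.5² = 7.1, so 8 per arm). That is a separate matter. The number 15 is used here only as the plan's own count of expected completers.

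**Assumed, because the article does not give them.** Let *m* be the share of the benefit that the immediate arm still has at week 16. Let *w* be the share that the waitlist arm has gained by then. Any change over time unrelated to treatment is the same in both arms in expectation.

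**Expected differences** (positive favours the immediate arm):

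- Week 8: 1.45 − 0 = 1.45 SD. This is the effect against an untreated arm.
- Week 16: (*m* − *w*) × 1.45.

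| Assumed truth | *m* | *w* | Week-16 difference (SD) |
|---|---|---|---|
| Works equally in both arms and lasts | 1 | 1 | 0 |
| Both arms end with half the benefit | 0.5 | 0.5 | 0 |
| Lasts; waitlist arm has half the benefit so far | 1 | 0.5 | 0.5 × 1.45 = 0.73 |
| Immediate arm loses half; waitlist arm gains in full | 0.5 | 1 | −0.5 × 1.45 = −0.73 |
| Rewind does nothing | – | – | 0 |

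Three different truths give 0, so the week-16 difference cannot tell them apart. Week 8 can separate an effective treatment from an inert one.

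**Chance of a significant result**, from an unadjusted two-sided 5% t test with 15 completers per arm: 97% for a difference of 1.45 SD, 48% for 0.725 SD, and 5% for 0. A Rewind effect that is fully kept would therefore be missed at week 16 about half the time if the waitlist arm is halfway there, and would be undetectable if it has caught up. Baseline adjustment would change these values but not the zero.

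**Maintenance.** Only the immediate arm (20 of 40 randomised) has two outcome visits after starting treatment. Its change from week 8 to week 16 is the direct evidence on objective 2. The 95% CI half-width in SD units is t(0.975, 14) × √(2(1 − r)) / √15, with r the assumed correlation between the two visits and equal SDs assumed:

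- r = 0.8: 0.35 SD, which is 0.35/1.45 = 24% of the benefit
- r = 0.5: 0.55 SD, which is 0.55/1.45 = 38% of the benefit

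The estimate is usable but imprecise, and it has no control.

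**The case against.** The strongest reply is that no sentence commits the sponsor to an efficacy comparison at week 16. The abstract gives times for an outcome, section 2.9 names no visit, and sections 2.1 and 2.7 together can be read as making week 8 the controlled comparison and week 16 the follow-up. The trial is also exploratory and attaches no decision rule to week 16. This stands to a degree: the week-16 efficacy reading is an inference. What it does not remove is the primary status that the abstract gives to both visits, which nothing in the body corrects. If week 16 was meant as follow-up, it should not be primary.

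Three stronger readings are tempting, and the article does not support them.

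- A reader might infer that objective 2 has no analysis. A condensed article may leave that to the full protocol or analysis plan, and the data needed are collected, so the silence is not a fault.
- A reader might infer that the phase 3 trial will be sized from the week-16 difference. The Discussion speaks only of effect sizes in general and does not say which visit will be used.
- A reader might infer that the trial cannot show efficacy. It can, at week 8.

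**Conclusion.** The point holds as a fault in how the primary outcome is fixed. Only week 8 gives the randomised comparison with waitlist. At week 16 the arms differ in when treatment was offered, and the difference between them does not by itself measure efficacy or maintenance. Under the assumed shares it runs from −0.73 to 0.73 SD for the same true benefit of 1.45 SD, with 0 as the value for lasting success, for partial loss in both arms and for no effect at all.

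The conclusion itself rests only on the abstract and section 2.7. The sizes rest on the assumed *m* and *w*. It is also assumed that the week-8 assessment precedes the waitlist arm's first session. The harm is confined to week 16, and the remedy is cheap, so the sponsor should make the change, but the trial's main comparison is not in doubt.

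**What to change.** - Name week 8 as the single primary time point for the between-arm ANCOVA, in the abstract and in sections 2.6 and 2.9, and base the efficacy conclusion on it.
- Make week 16 secondary, and state that its between-arm difference is not read as efficacy.
- Address objective 2 with the immediate arm's mean CAPS-5 change from week 8 to week 16 and its 95% CI, labelled uncontrolled. Report the waitlist arm's change over the same interval separately, as an uncontrolled response to treatment.
- If an effect size is carried into the phase 3 power calculation, take it from week 8 and not week 16. Add a note that the future trial is to be against usual care, and that an effect against waitlist may overstate the effect there.

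The cost is wording and two within-arm estimates from data already collected, with no extra participants or visits. The downside is that week 16 is no longer a primary result, and the maintenance estimate is uncontrolled and imprecise.

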## Background and rationale

1.

Post-traumatic stress disorder (PTSD) is a common mental illness occurring after a traumatic event, with symptoms of re-experiencing, hyper-arousal, negative alterations in cognition and mood, and avoidance. It has been estimated that between 1.1% and 2.9% of EU adults suffer from PTSD (Wittchen et al., 2011) and the prevalence of PTSD in high-risk populations such as those exposed to certain types of interpersonal trauma, mass conflict and displacement are estimated to be much higher (Kessler et al., 2017; Steel et al., 2009). PTSD is associated with substantial physical and psychiatric co-morbidity, for example type 2 diabetes, ischaemic heart disease, somatic symptom disorder, substance abuse and suicide (Roberts et al., 2015) and research suggests that current psychological and pharmacological treatments remain ineffective in a substantial proportion of those with PTSD (Olff et al., 2019, Lewis et al. 2020). Trauma-focused psychological therapies in the form of individual trauma-focused cognitive behavioural therapy (TFCBT) and eye movement desensitisation and reprocessing (EMDR) are currently the most effective treatments for PTSD symptoms with pharmacological approaches effective but to a lesser degree (National Institute for Health and Care Excellence (NICE), 2018, Bisson et al. 2019). Sadly, many people with PTSD remain symptomatic, despite evidence-based treatment, partially due to high drop out rates in trauma-focused therapies, which appear particularly difficult to tolerate (Lewis et al. 2020). There is an urgent need to develop more effective treatments (Olff et al., 2019), which are shorter in duration and less emotionally distressing (Lewis et al. 2020).

The positive outcomes of recent studies of novel treatments have raised interest in the mechanism and study of memory reconsolidation and further work in this area is merited to establish the exact mechanism of action (Brunet et al., 2018; Gray, Budden-Potts, & Bourke, 2017). As memory reconsolidation has been specifically targeted by some novel treatments (Gray et al., 2017) which have many similarities to the Rewind technique (the psychological intervention assessed here) we will consider reconsolidation theory in detail below.

Memory consolidation is the process where short-term memories are converted into long-term ones, while in memory reconsolidation long-term memories are reactivated, changed and then updated. Memories of stressful and fearful events have a large degree of salience and so are laid down particularly concretely within the biology of the brain, giving rise to PTSD symptoms. Fearful memories are made in periods of high emotional arousal and the formation of these is strengthened by the stress hormones that contribute to initial memory consolidation. Cortisol (De Quervain et al., 2003) and adrenaline are released during periods of significant stress, and these regulate memory consolidation by causing noradrenergic excitement of the basolateral amygdala (McGaugh, 2015; Roozendaal & Hermans, 2017; Schwabe & Bolam, 2017). While this is not exclusive to fearful memories, and heightened memory consolidation occurs in a variety of emotional experiences, it is argued that disrupted memory consolidation plays a key role in the development and maintenance of the characteristic symptoms of PTSD, such as hyperarousal and re-experiencing (Pitman, 2019).

Despite this, emotional memory is highly malleable (Pitman, 2019) and a number of medications are believed to be able to interrupt reconsolidation, with the potential therapeutic effect of decreasing PTSD symptoms. Animal research has shown that neuroplasticity is not only required for the creation of new emotional memories but also for the removal of fear memories (Nader, Schafe, & Le Doux, 2000). The neuroplasticity of memory consolidation requires protein synthesis, a process which can be interrupted to prevent learning consolidation and create amnesia of a fearful event (Nader et al., 2000). Furthermore, when already consolidated fear memories are remobilised, new protein synthesis can facilitate reconsolidation, providing an opportunity to reconsolidate memories and decrease their emotional salience (Nader et al., 2000). Once a memory becomes reactivated and the memory is returned to a mobilised state similar to pre-consolidation, the protein synthesis antagonist anisomycin can be given to block this reconsolidation (Pitman, 2019). While anisomycin’s toxicity prohibits its use as a therapy in humans, its action provides understanding of how the mobilisation of fear memories may ameliorate PTSD symptoms (Suris, Smith, Powell, & North, 2014). While exposure-based therapies may inhibit the body’s reaction to the traumatic memory, or impair its retrieval (de Quervain, Schwabe, & Roozendaal, 2017), memory reconsolidation treatments aim to mobilise traumatic memories to remove these pathognomonic symptoms entirely (de Quervain et al., 2017; Pitman, 2019).

It may, however, not be necessary to use pharmacological approaches to augment/facilitate reconsolidation. Non-pharmacological approaches may also be effective and would likely be preferred and better tolerated by many people with PTSD (Feeny, Zoellner, & Shoshana, 2009), and avoid the contraindications for some pharmacotherapies (e.g. asthma with propranolol). Reconsolidation of Traumatic Memories (RTM) is a non-pharmacological approach that aims to treat PTSD through memory reconsolidation over three sessions (Gray, 2011). The proven mechanism of RTM remains unclear, however, and additional factors, such as the reactivation and redistribution of emotional memories in the neocortex during sleep, may also play a role (Schafer et al., 2020). RTM (Gray, 2011) has RCT evidence of effect leading to it being recommended as a treatment with emerging evidence by the ISTSS Treatment Guidelines for PTSD and for military populations (Bisson et al, 2019; Kitchiner, Lewis, Roberts, & Bisson, 2019). RTM is a development of the Rewind Technique, another non-pharmacological approach, with many similarities in its delivery to RTM, but with an evidence base that is currently reliant on non-randomised trials (Adams & Allan, 2018; Utuza,, Joseph, & Muss, 2012). RTM and Rewind both employ ‘rewinding’ techniques (where the participant plays their trauma memory in reverse) using different intervention protocols.

The Rewind Technique and RTM seek to briefly mobilise traumatic memories, before exploring dissociative experiences surrounding the trauma which are proposed to modify the memory, reconsolidating it so that it can be remembered without evoking PTSD symptomatology (Tylee, Gray, Glatt, & Bourke, 2017). The brief memory mobilisation stimulus is thought to be too brief to produce effects via improving the extinction of the traumatic memory (Merlo, Milton, Goozée, Theobald, & Everitt, 2014), and follow up suggests that the rapid reacquisition or reinstatement of traumatic memories, that might be expected if the underlying mechanism was one of memory extinction, does not occur (Gray et al., 2017).

Some reconsolidation approaches have yielded negative results (Bos, Beckers, & Kindt, 2014; Wood et al., 2015) highlighting the specific limitations which exist around the ability of a therapy to destabilise and modify a traumatic memory. These factors, such as the length of the memory reactivation procedure and the age and context of the traumatic memory, are known as boundary conditions (Treanor, Brown, Rissman, & Craske, 2017) and have complicated the process of translation from experimental into clinical settings. Promising preliminary evidence, however (Adams & Allan, 2018; Utuza, et al., 2012), suggests that if reconsolidation is the mechanism of action for the Rewind technique, that these conditions may have been met.

While trauma-focused psychotherapies (TFCBT, EMDR) have medium to large effect sizes, the therapy requires large amounts of therapist time (Lewis et al. 2020). We expect that Rewind will have a similar effect size, but be more time and cost efficient, delivering a trauma-focused intervention in just a few sessions. Furthermore, as Rewind is relatively simple to deliver it has potential to be delivered by lower intensity therapists and therefore is more easily scalable. Furthermore, evidence of multiple effective therapies also provides treatment choice for people with PTSD, e.g. some individuals may prefer Rewind as it does not require trauma disclosure. Considering this, Rewind may be most suitable as a first-line intervention as part of a stepped care approach.

Given the promise of non-pharmacological approaches to the treatment of PTSD through the mechanism of memory reconsolidation, we aim to undertake a preliminary efficacy RCT to determine if the Rewind Technique is likely to be a good candidate to test against usual care in a future pragmatic efficacy RCT. Our objectives are:

1. To investigate the effect sizes of the Rewind Technique at reducing PTSD symptoms in people with PTSD.

2. To establish whether any symptom improvement is maintained over 16 week follow up.

3. To investigate the impact of the Rewind Technique on symptoms of depression, anxiety and insomnia.

4. To investigate if an efficacy RCT is feasible and indicated.

5. To assess if the Rewind Technique is acceptable to participants with PTSD as measured by a qualitative questionnaire.

